### Data Monitoring

The eRegMat trial is considered to be a health systems research where the intervention aims only to support existing care processes for care providers and does not constitute a medical intervention for individual subjects. Hence, a formal data safety monitoring board was not established.

#### Harms

As such, we do not anticipate any harm from the introduction of the intervention. The introduction of new technology may have resulted in reduced efficiencies during the initial months of utilization; however, we expect this to have resolved before the data inclusion period of this trial.

#### Audit

The CISMAC was responsible for trial monitoring. An initial monitoring visit was conducted in June 2018 to assess readiness before the start of recruitment. Midway, monitoring was conducted in November 2019, when recruitment rates, fidelity to the intervention, and progress of data collection were assessed.

### Ethics and Dissemination

#### Ethics and Consent to Participate

This study was reviewed and approved in Bangladesh by the Research Review Committee and Ethical Review Committee of icddr, b (Ref: PR-16054) and by the Regional Committee for Health Research Ethics–South East B Section (Ref: 2017/1028 C) in Norway. All health workers using the eRegistry and their supervisors at the Matlab North and Matlab South Upazilas were notified of their participation in the trial by the Ministry of Health and Family Welfare. No financial incentives were provided to the health facilities or care providers involved in this study; participation was considered mandatory by the central government. Financial support for participating in training sessions and meetings was conducted according to the government guidelines.

Informed consent would typically not be warranted for health systems research studies using anonymous health data, but three features in the implementation of this trial required additional ethical considerations. First, national guidelines recommend that family welfare assistants perform a urine pregnancy test for women who are uncertain of their pregnancy status. Because test kits were often unavailable in the health system, they were provided to health workers for the purpose of this trial. Women’s consent was required to obtain a urine sample for pregnancy testing. The sample never left the home, and the results were strictly confidential. If the woman declined to provide her sample, then the health worker privately counseled the woman of her options for testing. Second, the woman’s consent was required to receive targeted client communication via SMS text message. Women were informed about the purpose of the service, the content of SMS text message reminders, measures to ensure data confidentiality, and their ability to opt out of the service at any time. Providing a mobile phone number was assumed to imply consent. The option to stop receiving SMS text messages was available at every encounter of clients with their health workers. Phone numbers were available only to health workers who had access to the client’s health records. Third, all women enrolled in the eRegistry were asked to provide informed consent to undergo a postpartum home visit. This consent was for the purpose of being contacted by the study team during the latter part of their pregnancy and to allow the study team to conduct a visit 8-14 days postpartum. If women themselves notified the study team of the culmination of her pregnancy, a small incentive of 100 taka (approximately US $1) was given at the time of the home visit as a token of appreciation.

#### Confidentiality

The eRegistry data will be managed in accordance with the Ministry of Health and Family Welfare governance policies for health information systems. All data are stored securely on the national server under the custodianship of the Ministry.

#### Access to Data

The eRegistry data are owned by the Ministry of Health and Family Welfare in Bangladesh and subject to their regulations and legislation. Only one legally authorized person in the Bangladeshi Ministry of Health and Family Welfare will have access to individual-level data in the eRegistry. At no point will the researchers have access to identifiable data of any kind. The postpartum household questionnaire database will not be available outside the standard analysis protocols of the project, in accordance with the data access protocols of icddr, b.

#### Protocol Amendments

Changes in the secondary outcomes were written as amendments to the trial registration after being agreed upon in the study group. Amendments that amount to significant modifications to the study design have been reported to the CISMAC.

#### Collaborative Arrangements

The Norwegian Institute of Public Health owns the project and is ultimately responsible for the overall conduct; the institute has agreements with all the research partners detailing their roles and responsibilities. The icddr, b was responsible for the implementation and administration of the trial in Bangladesh, whereas the University of Oslo was responsible for the development of the eRegistry software in collaboration with other partners.

#### Dissemination Plan

The SPIRIT (Standard Protocol Items: Recommendations for Interventional Trials) guidelines were followed for writing this protocol (Multimedia Appendix 2). The trial publication will follow the CISMAC rules for authorship and publication and the Bangladesh Ministry of Health and Family Welfare regulations. We will publish the results in peer-reviewed open access journals and report them in accordance with the CONSORT (Consolidating Standards of Reporting Trials) guidelines.

## Results

Implementation of the eRegistry started in April 2018, after preliminary field testing (Table 4). Data documentation in the eRegistry started after the health workers completed a second round of training between July and December 2018. Data on all women enrolled between October 2018 and June 2020 (21 months) will be included in the analysis. The follow-up ended in February 2021, when the last enrolled woman received a postpartum household visit. Approximately 8000 pregnancies were registered in the eRegistry during the trial. The results of the trial are expected to be available in July 2021.

**Table 4 table4:** Timeline of the eRegMat cluster-randomized controlled trial.

Implementation of the study		2018				2019					2020					2021
		Apr-May	Jul-Oct	Oct-Dec	Jan-Mar		Apr-Jun	Jul-Sep	Oct-Dec	Jan-Mar		Apr-Jun	Jul-Sep	Oct-Dec	Jan-Feb	

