#### Intervention Arm

In the intervention arm, the eRegistry supported 3 data-driven DHIs linked to the digital client health records (Table 1) as follows: (1) for facility-based staff, health worker clinical decision support based on national guidelines to promote the correct management of health conditions identified in antenatal care; (2) for both field- and facility-based staff, feedback dashboards tracking the health worker’s progress toward pregnancy registration, antenatal care attendance and utilization, and clinical screening and management targets; and (3) for pregnant women, targeted client communication in the form of SMS text messages to address gaps in the timely attendance of antenatal care visits and facility delivery. Following the initial implementation of the eRegistry, the DHIs in the intervention arm were gradually introduced over the course of the trial; health worker clinical decision support was introduced in October 2018; targeted client communication via SMS and feedback dashboards were implemented in June 2019. Digital client health records were accessible across the cadres of health workers, facilities, and arms of the health system for a comprehensive longitudinal tracking of clients’ health status and services received (Table 1).

Guideline-based clinical decision support and feedback dashboards were developed in close collaboration with health workers. The decision support comprised referral and counseling reminders, medication alerts, and scheduling based on the recommended guidelines in the public health system. Feedback dashboards were customized for each cadre of health workers, with indicators of antenatal care attendance and screening and management of gestational diabetes, hypertension, and anemia. Targeted client communication included SMS text message reminders of routine antenatal care, referral facilitation SMS text messages for those at risk, and facility delivery reminders for those who are advised to have an institutional delivery. All DHIs were triggered by data entry into the eRegistry at the point of care by the health workers.

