### Outcomes

The outcomes were formulated based on their relevance to the health system context and were meant to capture the potential effects of the specific DHIs under assessment. Data for the primary (Table 2) and secondary outcomes (Table 3) will be derived from the eRegistry’s client health records and through postpartum home visit interviews.

**Table 2 table2:** Primary outcomes, data sources, and definitions.

Primary outcome	Sources of data	Measurement sequence	Definition	Intervention subcomponents with most direct effect
Timely attendance at eligible ANC^a^ visits	Postpartum household survey	Registrations continuously at point of care Household visit after the completion of pregnancy	Proportion with timely attendance	Targeted Client Communication via SMS text message: ANC appointment reminders
Screening and management for hypertension in pregnancy	Case records from the eRegistry^b^	Registrations continuously at point of care	Proportion that has at least one ANC at a randomized health facility with: Blood pressure measurement at routine ANC visits, and Referred if blood pressure is high, or Referred if blood pressure is high outside of the routine ANC visit	Health worker clinical decision support Feedback dashboards with action items

^a^ANC: antenatal care.

^b^eRegistry: electronic registry.

**Table 3 table3:** Secondary outcomes, data sources and definitions.

Secondary outcome	Sources of data	Measurement sequence	Definition	Intervention subcomponents with assumed direct effect
Timely first ANC^a^ visit	Case records from the eRegistry^b^ Postpartum household survey	Registrations continuously at point of care Household visit after the completion of pregnancy	Proportion of women that have an ANC visit at or before 16 weeks among those with a home pregnancy registration before 16 weeks	Targeted Client Communication via SMS text message: ANC appointment reminders
High-risk women successfully referred to a skilled provider for additional care	Case records from the eRegistry Postpartum household survey	Registrations continuously at point of care Household visit after the completion of pregnancy	Proportion of women that received additional care during pregnancy among those that are referred for severe anemia, or hypertension or diabetes during pregnancy	Health worker clinical decision support Targeted client communication via SMS: Referral reminders, high risk, facility delivery reminders

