### Data Collection

#### Overview

The eRegistry used by health workers in the intervention and control arms will provide some of the data for outcome measurements. Independent trained project staff collected data regarding birth outcomes, antenatal care utilization, and referral care seeking from a subset of the population of registered pregnancies through a postpartum household survey. The postpartum household survey started in June 2019, 8 months after the commencement of recruitment. Data collectors were provided with a list of all pregnancies registered in the eRegistry that were beyond 28 weeks of gestation at a given point in time. The data collectors made biweekly phone calls to clients from 28 to 35 weeks, and weekly thereafter to ascertain whether the pregnancy was ongoing. Postpartum household visits for data collection were conducted within 8-14 days of childbirth. A paper-based structured questionnaire was used for data collection (Multimedia Appendix 1), focusing on the experiences of pregnancy and childbirth, health care interventions received, and health outcomes of the mother and the newborn. The infant’s weight was measured during the home visit; weight was measured in minimal clothing, and the weight of the clothes was subtracted from the total weight. Where possible, women’s finger-prick blood was used to measure hemoglobin. The questionnaires were checked for completeness and consistency by the data collectors’ supervisors, and women were interviewed again if needed. Data from the paper questionnaires are being made electronic, and consistency checks are performed by the study team after data entry.

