**Intervention**																
	eRegistry^b^ (intervention and control)			✓	✓		✓	✓	✓	✓		✓				

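### The 21-month analysis cohort does not fit primary outcome 1: its only listed data source and its main driver, the SMS reminders, both began in June 2019, 8 months into enrolment

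*Protocol article*

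**What the plan says.** Under Results, the protocol article fixes the cohort: "Data on all women enrolled between October 2018 and June 2020 (21 months) will be included in the analysis". Statistical Methods makes the primary analysis intention-to-treat by allocated cluster.

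Under Intervention Arm, the roll-out is staged: "the DHIs in the intervention arm were gradually introduced over the course of the trial". Specifically, "health worker clinical decision support was introduced in October 2018", whereas "targeted client communication via SMS and feedback dashboards were implemented in June 2019".

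Under Outcomes, Table 2 gives one data source for timely ANC attendance, the postpartum household survey. The component it names as having the most direct effect is "Targeted Client Communication via SMS text message: ANC appointment reminders". For the hypertension outcome, the source is the eRegistry and the components are decision support and dashboards.

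Under Data Collection, Overview: "The postpartum household survey started in June 2019, 8 months after the commencement of recruitment". Visits take place 8-14 days after birth, and the data come "from a subset of the population of registered pregnancies through a postpartum household survey".

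Sample Size assumes 77 women (140 contacts) per cluster over the 21 months, an intracluster correlation of 0.1, and changes from 20% to 33% and from 12% to 22%, with power above 80%.

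**The concern.** These statements do not fit together for outcome 1.

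First, a woman who delivered before the survey began has no listed source for timely attendance. Including every woman enrolled from October 2018 is therefore not possible for this outcome, and the article does not say which women remain.

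Second, women who enrolled early but were still pregnant in June 2019 can be surveyed, yet some of their visits fell due before any reminder could be sent. Those visits count in the intervention arm as if the full package had been in place, and they pull the estimate towards no effect. The sample size uses the undiluted 13-point difference, and no analysis in Statistical Methods separates the periods before and after launch. The per-protocol and dose-response analyses there turn on where and how often women attended, not on calendar time.

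At stake is how a weak or null result on outcome 1 would be read: it could not distinguish reminders that do not work from reminders that had not yet started.

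**Working it through.** **Inputs from the article.** Enrolment October 2018 to June 2020; SMS and survey from June 2019; 30 and 29 clusters (29.5 per arm used); 77 women per cluster; intracluster correlation 0.1; 20% versus 33%.

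**Assumptions, not in the article.** Two-sided 5% level. Enrolment uniform from 1 October 2018 to 30 June 2020. SMS and survey start on 1 June 2019. Birth at 40 weeks. Registration uniform over one of four ranges within 6-28 weeks. Four ANC windows, each reduced to one time point (14, 26, 32 and 36 weeks) and eligible if it falls after registration. In the worst case, the effect is zero before SMS.

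**Step 1: the stated power.** With design effect DE = 1 + (m − 1) × 0.1 and n = 29.5 × m / DE per arm, power = Φ{(p2 − p1)/√[(p1(1 − p1) + p2(1 − p2))/n] − 1.96}.

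For m = 77: DE = 8.6 and n = 264.1. The standard error is √[(0.1600 + 0.2211)/264.1] = 0.0380. Then 0.13/0.0380 = 3.42, and Φ(3.42 − 1.96) = 0.93. The stated figure of more than 80% reproduces.

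**Step 2: enrolment time before launch.** 243 of 638 days, or 38% (8 of 21 months). This is a share of enrolment time, not the dilution, because many of these women were still pregnant in June 2019.

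**Step 3: unmeasured women, and dilution among the rest.** Of 77 women per cluster, only those delivering after survey start stay in m. The diluted rate is p2 = 0.20 + 0.13 × f, where f is the share of their windows falling after launch.

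| Registration (weeks) | Delivered before survey | Windows before SMS, surveyable women | m | p2 | Power |
|---|---|---|---|---|---|
| 6-14 | 5.2% | 15.1% | 73.0 | 0.310 | 83.3% |
| 8-20 | 9.5% | 13.4% | 69.7 | 0.313 | 84.4% |
| 10-24 | 12.8% | 12.8% | 67.1 | 0.313 | 84.8% |
| 12-28 | 16.1% | 11.9% | 64.6 | 0.315 | 85.2% |

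Across these ranges, 19-30% of surveyable women have at least one window before launch.

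**Step 4: a second model.** All women register at one gestation between 6 and 28 weeks, and the effect is proportional to the share of remaining pregnancy after launch. The unmeasured share is then 1% to 25%, and power among surveyable women is 80% to 87% (79.8% at the extreme where all register at 6 weeks).

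**Step 5: counting only post-launch windows.** Under the Step 3 assumptions, 80-90% of enrolled women keep at least one countable window (m from 61.2 to 69.7). Power for the undiluted 20% versus 33% is 92.2% to 92.6%. Little is lost because, at an intracluster correlation of 0.1, power depends mainly on the number of clusters.

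**The case against.** The staged roll-out and the survey's partial coverage are both disclosed. Intention-to-treat over a staged roll-out is a legitimate estimand (the package as implemented), and its dilution is conservative. The survey gap follows the same calendar in both arms, so it mainly costs sample and is not in itself a bias between arms. Table 2 names the most direct effect, not the only one: decision support, live from October 2018, included scheduling, and intervention-arm records were shared across cadres. If pre-launch windows carried a quarter of the effect, p2 at f = 0.85 would be 0.20 + 0.13 × (0.85 + 0.25 × 0.15) = 0.315 and power about 86%. Detailed analysis sets often sit in an analysis plan not shown here.

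Most of this stands, and it limits the size of the problem. It does not remove the conflict, because the article positively states a set that outcome 1 cannot use.

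A reader might go further and infer that the trial falls below its stated power. Counting every enrolled woman's windows does give 66-79% in the second model, but that includes women who delivered before the survey. They have no outcome 1 data and cannot also dilute it, unless they are imputed, which the article only says will be considered. Lower figures still can be had by taking Table 4 to mean that the eRegistry stopped in June 2020. The text has follow-up to February 2021, and the table's columns may be damaged in extraction, so it cannot carry a power figure.

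Outcome 2 is less affected: its data come from the eRegistry, and only the dashboards were late.

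**Conclusion.** The point holds for outcome 1 as an undefined analysis set and a moderate, avoidable dilution. About 5-16% of enrolled women have no outcome 1 data, and about 12-15% of the windows of surveyable women fell before SMS launch. Power for 20% versus 33% drops from about 93% to about 83-85% if SMS carries the whole effect, and by less if decision support contributes. The stated power is eroded, not undone.

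These sizes rest on uniform enrolment, an assumed window timing and, above all, gestation at registration, which the article does not give. The contradiction between the stated cohort and the survey start rests on none of these assumptions.

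**What to change.** 1. Define the outcome 1 analysis set as women whose expected delivery date falls after survey start, with the same calendar rule in both arms. Using the expected rather than the actual date avoids selecting on early birth; women in the set who delivered before the survey are then counted as missing.
2. Before unblinding, prespecify an analysis of outcome 1 that counts only ANC windows opening on or after SMS go-live, with the same cut in both arms and without regard to individual SMS receipt. Report it beside the intention-to-treat estimate.
3. Add a matching June 2019 cut as a sensitivity analysis for outcome 2.
4. State whether the primary estimand is the effect of the staged roll-out or of the full three-component package.
5. Restate cluster size and power for the set actually used.
6. Check the enrolment and eRegistry end dates in Table 4 against the text.

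The cost is wording, a little more analysis, and about 5-20% fewer women in the outcome 1 analyses: 5-16% under the survey-start rule and 10-20% under the post-launch rule. The post-launch analysis keeps about 92% power for the full effect. No new data are needed.

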**Enrollment**																
	Trainings	✓^a^	✓				✓									
	Enrollment			✓	✓		✓	✓	✓							
**Intervention**																
	eRegistry^b^ (intervention and control)			✓	✓		✓	✓	✓	✓		✓				
**Assessment or follow-up**																
	Outcome data collection			✓	✓		✓	✓	✓	✓		✓	✓	✓	✓	

^a^Period during which the trial activity was conducted.

^b^eRegistry: electronic registry.

## Discussion

### Study Relevance

There is a global trend toward digital data collection in health systems in LMICs; however, the collected data are rarely used to support multiple DHIs. DHIs are shown to have relatively modest effects on their own, whereas a package of several simultaneously delivered DHIs is likely to be more effective and cost-effective. We designed a trial that compared two types of digital data collection systems: one where the longitudinally collected individual-level data in an eRegistry does not drive additional DHIs (control arm) and one where the data entered are used to generate three additional DHIs (intervention arm).

Antenatal care utilization in Bangladesh is suboptimal, with only 37% reported attendance of four or more visits [15]. In addition, gaps in antenatal care content and quality have been highlighted in studies conducted in other parts of Bangladesh [21]. The eRegistry’s data-driven DHIs aim to address antenatal care utilization (through targeted client communication via SMS text messages) as well as the quality of care (through health worker clinical decision support based on national guidelines), thereby addressing the two essential components of the effective coverage of antenatal care [22].

The transition of clinical documentation from paper to electronic data entry in digital client records may affect clinical practices and health care service delivery, even without any additional DHIs such as clinical decision support. In our trial, we wanted to evaluate the effects of data-driven DHIs per se, while controlling for the possible effects of the transition from paper to digital systems. Consequently, the control arm of the trial uses the eRegistry, albeit only as a digital data entry tool, with no superimposed DHIs.

The different government health workers in Bangladesh largely operate in silos, which limits the use of routinely reported data. The eRegistry spans multiple cadres of health workers and departments of the health system. The use of an eRegistry purposefully implemented for use by all cadres of health workers who typically meet an individual client in the public health system can provide more reliable data and improve the quality of health services. Health workforce capacity is an important component of the enabling environment for digital health [23]. In our study setting, except for the community health care providers, the other cadres were not skilled in using digital tools. Furthermore, health care workers do not receive in-service training in the use of digital tools. Low technology skills and lack of in-service training in the use of digital tools are common issues in several LMICs [24]. In addition to the results of the trial, we will report on the delivery of different components of the intervention, training needs, and implementation support over the course of the study. Such reporting would not only be in line with the general recommendations of reporting of trial of health systems and of DHIs [25] but also serve as useful guides for others planning studies of DHIs for health system strengthening in comparable health system settings.

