### Objectives

The objective of this eRegistry trial (eRegMat) in Matlab, Bangladesh, is to assess the effect of an eRegistry with DHIs compared with a simple digital data entry tool without any DHIs in the community and frontline health facilities.

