## Methods

### Trial Design

The eRegMat study is a two-arm cluster-randomized controlled trial. The unit of randomization is the primary care health facility, community clinics, and family welfare clinics. All pregnant women enrolled in the trial had their health information entered into the eRegistry. The intervention arm received 3 DHIs supported by the data in the eRegistry: (1) health worker clinical decision support, (2) feedback dashboards with action items, and (3) targeted client communication. The control arm received only a digital data entry tool without any additional DHIs.

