#### Control Arm

In the control arm of the trial, the eRegistry comprised only digital client health records (Table 1). The data points included in the client records were almost identical to the paper-based client records, and drop-down lists were added to some data points to optimize the use of the digital data entry tool. The eRegistry in the control arm was set up such that control users had no access to client records entered by other users. Apart from basic data validation warnings, data-driven DHIs were not available in the control arm (Table 1).

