#### Statistical Methods

The primary analyses will be conducted as an intention-to-treat analysis, based on the allocation question rather than the actual site of antenatal care services, comparing the intervention arm with the control arm for all outcomes. Health worker characteristics such as gender, age, and education and health facility characteristics such as distance to referral unit, volume of pregnant women seen per month, digital competency, and internet connectivity will be presented. Pregnant women’s age, parity, socioeconomic status, and education will be presented as background characteristics. Primary analyses will be performed at the individual client level. Categorical variables will be analyzed using generalized linear models of the binomial family with a log link to estimate the relative risks and prevalence ratios. Random effects will be included to account for the inherent effect of clustering. Absolute and relative differences between the intervention and control groups with 95% CIs were calculated. Confounders will be adjusted for in the primary analysis only if there are important baseline imbalances (ie, when the effect measure changes by more than 5% when added to the model). Subgroup analyses will be performed based on categories defined as a priori, such as those related to demographic characteristics. We will present the equity analyses of the differential effectiveness across subgroups, including wealth quintiles, residence, educational levels, and employment status for each outcome. The imputation of missing data will be considered.

To understand the client base and their utilization of the health system, we will describe the client flow across providers, facilities, and arms of the trial. It is expected that some women will cross between the intervention and control clusters to receive health care services. Secondary analyses will be performed per protocol, where only the subset of women who remain in their assigned clinic type (ie, all visits are within the intervention group or control group) will be analyzed. We will perform a dose-response analysis (based on the proportion and number of visits to the intervention group) to assess whether there is a threshold or linear effect based on the increased utilization of intervention clusters. Finally, we will present population-level estimates of the impacts of the eRegistry if they were to be fully implemented in this community.

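### The arms differ in access to client records as well as in the three named DHIs, so the trial estimates the effect of the whole package and not of the DHIs alone

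*Protocol article*

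**What the plan says.** Study Relevance gives the reason for a digital control arm: "we wanted to evaluate the effects of data-driven DHIs per se", with the move from paper to digital records controlled for. Trial Design describes the difference between arms in the same terms: "The intervention arm received 3 DHIs supported by the data in the eRegistry", against a control arm with the data entry tool and nothing added. The formal objective is wider. It is to "assess the effect of an eRegistry with DHIs compared with a simple digital data entry tool without any DHIs".

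The descriptions of the arms contain one more difference. Under Control Arm: "The eRegistry in the control arm was set up such that control users had no access to client records entered by other users". Under Intervention Arm: "Digital client health records were accessible across the cadres of health workers, facilities, and arms of the health system". Table 1 gives sight of everyone's records its own row, for the two facility cadres (community health care providers and family welfare visitors), and ticks it for the intervention arm only. Finally, Statistical Methods promises "population-level estimates of the impacts of the eRegistry if they were to be fully implemented in this community".

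**The concern.** A contrast isolates the DHIs only if the rest of the eRegistry is the same in both arms. Here it is not. One arm works with a shared longitudinal record, and in the other each user is confined to their own entries. A facility worker who can read what a colleague recorded, such as an earlier visit date or a referral, might act differently without any alert, dashboard or text message.

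At stake is what the result may be said to show. The abstract directs the findings at guidance on implementing DHIs. A ministry deciding whether to adopt decision support, dashboards and SMS needs to know that the comparator lacked shared records as well as those three tools. Opening records across users is a separate decision that needs none of them.

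**Working it through.** The question is mainly one of setting the passages side by side; a short power check follows.

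**1. What each arm has**

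| Component | Control | Intervention | Named as a DHI in Trial Design? |
|---|---|---|---|
| Digital data entry (Overview; Control Arm) | yes | yes | no |
| Own records (Table 1) | yes | yes | no |
| All records in the system, facility cadres (Table 1; Control Arm; Intervention Arm) | no | yes | **no** |
| Decision support | no | yes | yes |
| Feedback dashboards | no | yes | yes |
| SMS to women | no | yes | yes |

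Four rows differ between arms, and three of them are the named DHIs. (Table 1 also ticks facility-level digital client records for the intervention arm only, while Overview and Control Arm give them to both arms. Those places need reconciling, but nothing here rests on that row.)

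**2. Is shared access part of a DHI by the protocol's own terms?** No. The Background treats tracking a client's status over time as the core of an eRegistry, and the DHIs as what is added to it. The Intervention Arm section lists the three DHIs first and describes cross-cadre access separately.

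**3. Does the protocol treat shared access as something that could matter?** Yes. Study Setting notes that the paper system had no exchange between cadres. Study Relevance says that working in silos limits the use of data. Strengths and Limitations counts the single cross-cadre record as a strength, and its limitations do not mention that it is bundled with the DHIs. Tables 2 and 3 link each outcome to named DHIs and none to shared access.

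**4. Can the design separate the two?** No. There are two arms, with 30 + 29 = 59 clusters, and access follows arm in every one. The staggered rollout does not help. Decision support began in October 2018, when recruitment began, and the other two DHIs in June 2019, but no start date is given for shared access. No documented period has one without the other.

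**5. Does the sample size change?** The inputs are those in Sample Size (ICC 0.1; 77 women or 140 contacts per cluster; 20% to 33% and 12% to 22%), with 30 and 29 clusters. Two-sided alpha of 0.05 is my assumption, since the section does not state it.

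- Design effect = 1 + (m − 1) × ICC. For m = 77: 1 + 76 × 0.1 = 8.6.
- Effective n: 29 × 77 / 8.6 = 259.7 (control); 30 × 77 / 8.6 = 268.6 (intervention).
- Timely visits: SE = √(0.20 × 0.80 / 259.7 + 0.33 × 0.67 / 268.6) = 0.0379; 0.13 / 0.0379 = 3.43; power = Φ(3.43 − 1.96) ≈ 93%.
- Hypertension: SE = √(0.12 × 0.88 / 259.7 + 0.22 × 0.78 / 268.6) = 0.0323; 0.10 / 0.0323 = 3.09; power = Φ(3.09 − 1.96) ≈ 87%.
- With m = 140 (design effect 14.9), about 94% and 89%.

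The stated power of more than 80% is reproduced. It applies to the whole difference between arms, so relabelling that difference leaves it unchanged.

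**6. How much is unresolved?** The document gives no share for shared access. Assume, for illustration only, that contributions add and none is negative. Then the DHI part of the planned effects could lie anywhere from 0 to 33 − 20 = 13 percentage points for timely visits, and from 0 to 22 − 12 = 10 for hypertension. The trial cannot narrow either range.

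**The case against.** The best defence has three parts. First, the objective in the abstract and under Objectives compares an eRegistry with DHIs against a simple data entry tool, and randomization answers that question whatever is in the package. This stands. Second, the *per se* sentence goes on to say that the transition from paper to digital is being controlled for, which the control arm does, and the next sentence calls the control a data entry tool only. The wording is therefore loose rationale in a discussion, not an estimand. This softens the point, but a reader will still take the sentence to mean that the DHIs are isolated. Third, the difference is disclosed in Table 1 and in both arm descriptions. That is true, but disclosing a component in Methods is not the same as carrying it into the stated contrast or the limitations.

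Several stronger readings are tempting and should be resisted.

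- *Any effect would be credited to the wrong component.* The document shows only that attribution is not possible. Shared access might contribute nothing. For the hypertension outcome, measuring blood pressure and referring when it is high do not require another user's earlier reading.
- *The planning figures show how often shared records would matter.* Sample Size gives 140 contacts per 77 women, or 140 / 77 = 1.82 each, but this does not say how many different users a woman meets. Study Setting says that a typical facility has one permanent clinical cadre, and control users kept their own records.
- *The population-level estimate contradicts the design because both arms have an eRegistry.* It follows analyses of crossover and of visits to intervention facilities, so it most naturally means the intervention version. It is ambiguous, not wrong.
- *Comparing women seen by one user with women seen by several would separate the components.* That split conditions on care-seeking after randomization, which the SMS reminders are meant to change.

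**Conclusion.** The point holds as a mismatch between the stated contrast and the design. What is estimated is the effect of three DHIs plus shared record access, compared with digital data entry limited to the user's own records. The claim to evaluate the DHIs *per se*, and the description of the arms as differing by three DHIs, are not supported. The package objective is still validly answered.

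The size is qualitative: the share due to shared access is unknown, may be nil, and cannot be recovered from two arms. Power, sample size and primary model stand. The conclusion rests on taking Table 1 and the two arm descriptions at face value, that is, on the access setting having operated as written throughout the trial. It matters enough to correct before results are reported, because it changes what they may be said to show about DHIs.

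**What to change.** Make these wording changes:

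- **Trial Design and Intervention Arm:** name shared access to client records as an arm-specific component alongside the three DHIs.
- **The contrast, wherever it is stated:** three DHIs plus shared records versus own-record digital data entry.
- **Study Relevance:** replace the *per se* aim with the effect of this package, keeping the statement that the move from paper to digital is controlled for.
- **Strengths and Limitations:** add that shared access is bundled with the DHIs and that the trial cannot apportion an effect between them.
- **Statistical Methods:** say that the population-level estimate is the impact of adding this package to digital data entry.

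No new data or analyses are needed, and since recruitment has ended the design cannot be changed. The downside is a less specific claim about the DHIs.
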